#### Cortisol Analyses

To study the difference between morning and evening values, the evening-morning cortisol quotients will be calculated by dividing each girl’s evening cortisol value by the morning cortisol value. To study potential changes in evening-morning cortisol quotients between baseline and 4 and 8 months, the median change score will be calculated by subtracting baseline cortisol morning samples from 4-month morning cortisol samples and 8-month morning cortisol samples, and the same procedure will be performed for the evening samples.

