#### Sample Size

The total number of required study participants was calculated for the primary outcome (decreased maximal pain after 8 months). The calculation was based on several assumptions. First, we considered the expected proportion of participants who decreased their maximal pain after 8 months in the intervention group. We estimated that 30% of the intervention group would decrease their maximal pain after 8 months based on previous research with CBT, in which approximately 50% of participants were pain free immediately after the intervention [79]. Second, we calculated the expected proportion of participants whose maximal pain would decrease after 8 months in the control group. In previous CBT studies, approximately 25% of control participants reported being pain free when the intervention ended [79]. Since only girls with a long duration of abdominal pain were included in the present study, we estimated that the placebo effect would be smaller and that 10% of the girls in the control group would report decreased maximal pain at the 8-month follow-up. Third, dropout is a common problem that can bias outcomes. A 20% to 50% dropout rate is commonly reported in studies of participants with long-lasting pain [80]. In the present study, a 20% dropout rate was estimated.

With a power of 80% and a significance level of .05, we calculated the sample size to be N=150 (75 intervention + 75 control participants), including a 20% dropout. To decrease bias, a minimum of 50 participants in each group is recommended in trials studying intervention effects on pain, according to previous literature [80].

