##### Mental Health and Stress

Depressive symptoms are measured with the Children’s Depression Screener (ChilD-S). The ChilD-S is an 8-question validated screening instrument for depressive symptoms designed for children aged 9 to 12 years [95,96]. The recommended cutoff for depression is ≥13 when the child is investigated in psychiatric or psychosomatic care, according to the Swedish translation of the ChilD-S.

The questionnaires also include 8 questions about stress, anxiety, mood, and happiness. These questions are derived from the LH-YP [91].

Stress was also measured with salivary cortisol. Saliva was collected using oral polymer swabs and tubes (Salimetrics LLC). To measure the morning and evening components of the cortisol circadian rhythm, saliva was sampled as soon as possible after awakening while still in bed in the morning and at least 1 hour after last food intake in the evening on a weekday. Collection times were noted. Saliva cortisol has previously been used as a marker of stress for infants, youth, and adults within the research group (eg, with 11- to 12-year-old girls) [97]. The samples were centrifuged and stored at –20 ⁰C in the university hospital in Örebro and then sent on dry ice to the laboratory at the university hospital in Linköping, where they will be analyzed using a commercial enzyme immunoassay method (Salivary Cortisol Enzyme Immunoassay Kit; Salimetrics LLC) [98]. The results will then be sent back to Örebro University Hospital for evaluation.

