### Analyses

#### Statistical Analysis

The Just in TIME study follows the intention-to-treat paradigm. Complementary analyses will be performed per protocol and according to the number of sessions the participant attends.

For baseline statistics between the groups, descriptions will be constructed using frequencies and proportions for categorical data and means and standard deviations for continuous variables. Baseline characteristics will be compared using the Fisher exact test for dichotomous outcomes, the Mantel-Haenszel chi-square test for ordered categorical outcomes, and the Mann-Whitney U test or unpaired *t* test for continuous outcomes. A *P* value of <.05 for the 2-tailed test will be considered statistically significant for all outcomes. When deemed necessary, correction for multiple significance will be performed.

The primary outcome analysis will initially be performed using a Fisher exact test to evaluate differences between groups. To analyze the change in scores from baseline between groups for approximately normally distributed variables, a repeated-measures covariance pattern mixed model will be used, adjusting for significant differences at baseline. To identify predictive factors at baseline that might be associated with the primary outcome, a univariable logistic regression analysis followed by a stepwise multiple logistic regression analysis will be performed.

The distribution of continuous variables will be described using the mean and standard deviation or median and interquartile range. Categorical variables will be described with numbers and percentages.

Study participants who choose to leave the intervention before the study is finished are encouraged to complete all assessments. Missing data will be handled with multiple imputations or within the mixed model.

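### The only cortisol change measure is an unadjusted difference from baseline, which is less precise than adjusting for each girl's own baseline and does not measure change in the quotient it is meant to study

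*Protocol article*

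**What the plan says.** Under Cortisol Analyses, the article first defines an evening-morning quotient for each girl. It then states a purpose, "To study potential changes in evening-morning cortisol quotients between baseline and 4 and 8 months", and a calculation: "the median change score will be calculated by subtracting baseline cortisol morning samples from 4-month morning cortisol samples and 8-month morning cortisol samples". The evening samples are handled in the same way. The section names no arm comparison, test, model or covariate.

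Under Statistical Analysis there is a general rule: "To analyze the change in scores from baseline between groups for approximately normally distributed variables, a repeated-measures covariance pattern mixed model will be used". The treatment of baseline comes in the same sentence: "a repeated-measures covariance pattern mixed model will be used, adjusting for significant differences at baseline". The article does not say whether cortisol falls under this model.

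Under Mental Health and Stress, saliva is taken once on waking and once "at least 1 hour after last food intake in the evening on a weekday". This reads as one morning and one evening sample per time point. Cortisol is a secondary measure, and the article gives no power calculation for it.

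**The concern.** A single saliva sample is a noisy measure of a girl's usual level. The Discussion also concedes that compliance with the sampling instructions for cortisol cannot be verified. Subtracting the whole baseline value carries its noise into the outcome. Using baseline as a covariate removes only the part that predicts follow-up. Minimization used pain intensity and age, so nothing in the design balances cortisol between the 64 and 57 girls allocated. If one arm happens to start higher, its change scores will tend to fall more.

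The general mixed model does not settle this. Adjusting only after a significant baseline difference misses the main gain, which comes from baseline being prognostic and not from imbalance. If baseline were instead one of the repeated responses, with unconstrained arm-by-time means and complete data, the arm contrast would be the same as that of the change score.

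The calculation also does not match its stated purpose: it subtracts morning and evening values separately, although the target is a change in their quotient.

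**Working it through.** **The plan's own figure.** The article has no power or sample size for cortisol. Its only such figure is for the primary outcome: "With a power of 80% and a significance level of .05, we calculated the sample size to be N=150 (75 intervention + 75 control participants", including 20% dropout, for 30% against 10%. The arcsine formula gives 60 per arm, and 60/0.8 = 75 per arm, so N = 150 is reproduced. It has no bearing on cortisol.

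**Inputs for the precision check**
- Two-sided significance level of .05 (Statistical Analysis).
- Reference power of 80%. This is an assumption, used only as a yardstick.
- Correlation rho between baseline and follow-up. It is not in the documents, so a range of 0.3 to 0.9 is assumed.
- Equal SDs at baseline and follow-up, and a comparison of means. Both are assumptions.

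**Formulas**, relative to the variance of a comparison of follow-up values alone:
- Change score: 2(1 − rho)
- Adjusted for baseline (ANCOVA): 1 − rho²
- Ratio, adjusted to change: (1 − rho²) / [2(1 − rho)] = (1 + rho)/2
- Power of the adjusted analysis at an effect the change score detects with 80% power: Φ[(1.96 + 0.842)/√ratio − 1.96]
- Extra girls the change score needs for equal precision: 1/ratio − 1

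| rho | Change | Adjusted | Ratio | Adjusted power (change score 80%) | Extra girls |
|---|---|---|---|---|---|
| 0.3 | 1.40 | 0.91 | 0.65 | 93.5% | 54% |
| 0.5 | 1.00 | 0.75 | 0.75 | 89.9% | 33% |
| 0.7 | 0.60 | 0.51 | 0.85 | 86.0% | 18% |
| 0.9 | 0.20 | 0.19 | 0.95 | 82.0% | 5% |

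From the other direction, where the adjusted analysis has 80% power, the change score has about 62%, 68%, 73% and 78% at the same four values of rho. The ratio is below 1 for every rho below 1. Compared with the follow-up value alone, the change score is noisier below rho 0.5, equal at 0.5 and more precise above it.

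**Check of the target quantity.** Take invented values for one girl: morning cortisol goes from 10 to 8 and evening cortisol from 2 to 1.6. The planned differences are 8 − 10 = −2 and 1.6 − 2 = −0.4. The quotient is 2/10 = 0.20 before and 1.6/8 = 0.20 after. Both planned differences show a fall, yet the quotient has not changed. Taking medians of the two differences separately also loses the pairing within each girl, so the change in the quotient cannot be recovered from them. This part needs no assumption about rho.

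**The case against.** The strongest objection is that the cortisol section does not fix an arm comparison at all. A median change can be plain description, and the comparison may be left to a fuller plan that is not shown. That stands. A reader might infer that the plan chose change scores in place of baseline adjustment for testing the arms, but the text does not say so. A reader might also infer from the use of a median that cortisol is excluded from the mixed model. That is not stated either, and the model could be applied, for example after transformation. What remains is that the difference is the only change measure given, and that neither section, followed as written, guarantees adjustment for baseline.

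A second tempting reading is that regression to the mean biases the result. It does not: over randomization the change-score contrast is unbiased. Sensitivity to a chance baseline imbalance is real for the sample drawn, but it is already part of the variance penalty and should not be counted again.

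A third is that a large loss of power has been shown for this trial. It has not. Rho is unknown, the 80% is a yardstick, and the formulas are for means with equal SDs. They do not cover medians, or a raw change set against a log-scale model. Stress is also measured by questionnaire, so cortisol does not carry that question alone.

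**Conclusion.** The point holds as a modest matter of efficiency and of definition. A between-arm comparison built on the stated change score would be less precise than one adjusted for the girl's own baseline. Under the assumptions above, the variance ratio runs from 0.65 at rho 0.3 to 0.95 at rho 0.9, a gain of about 14 points of power falling to about 2 from an 80% reference. Where this trial lies in that range cannot be told from the documents. The outcome is secondary and unpowered. The mismatch between the quotient as target and the separate differences as calculation is the firmer part, because it follows from the text alone.

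**What to change.** Rewrite the cortisol rule as follows:
- Calculate the evening-morning quotient for each girl at each visit.
- Compare arms at 4 and 8 months on log quotient, log morning cortisol and log evening cortisol in the mixed model already named under Statistical Analysis, with arm, time and arm-by-time.
- Always include the girl's own baseline log value of the same quantity as a covariate, whether or not the arms differ significantly at baseline.
- Report arm effects as ratios of geometric means, and keep median changes as description only.

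This changes wording only and needs no new samples. The article describes the cortisol assays as still to be done, so on its account the rule could be changed before results are seen. The downside is that readers must interpret ratios of geometric means, where the present text would give them median changes in the original units.

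### The cortisol plan aims at change in the evening-to-morning quotient, but its change score takes differences in morning and evening levels separately, which do not determine that change

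*Protocol article*

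**What the plan says.** The Cortisol Analyses section of the protocol article makes three statements in sequence.

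- **Definition.** "the evening-morning cortisol quotients will be calculated by dividing each girl’s evening cortisol value by the morning cortisol value".
- **Target.** "To study potential changes in evening-morning cortisol quotients between baseline and 4 and 8 months".
- **Calculation offered for that target.** "the median change score will be calculated by subtracting baseline cortisol morning samples from 4-month morning cortisol samples", with the 8-month morning samples treated likewise. For the evening, "the same procedure will be performed for the evening samples".

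The Mental Health and Stress section lists cortisol among the secondary outcomes ("Stress was also measured with salivary cortisol"). It gives the reason for sampling twice a day: "To measure the morning and evening components of the cortisol circadian rhythm". Otherwise it covers collection, storage and assay. The Statistical Analysis section offers a general mixed model for change in approximately normal variables and does not mention the quotient.

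**The concern.** The second and third statements belong to one sentence and do not match. The target is a change in a ratio. The calculation yields two changes in level, one for the morning and one for the evening. The quotient is defined and then never used in a change score.

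If the sentence is followed literally, the reported figure would be presented as evidence on the quotient while measuring shifts in level. If the analyst sees the mismatch and departs from the text, three candidate change scores are available (morning, evening, quotient) and the protocol does not say which one answers the stated question. Such a choice should not be left open until the data are in hand.

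This is not a detail that an article leaves to a fuller document. The article does state a derivation, and the derivation does not deliver the quantity it is stated for.

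**Working it through.** The article states no cortisol figure, so there is nothing to reproduce. The question is whether the specified differences determine the quantity named as the target. All cortisol levels below are assumed, in arbitrary units.

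**Notation.** M is the morning level, E the evening level and Q = E/M the quotient as the Cortisol Analyses section defines it. Subscript 0 is baseline and t is 4 or 8 months.

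- Target: dQ = E_t/M_t - E_0/M_0.
- Specified: dM = M_t - M_0 and, separately, dE = E_t - E_0, summarised by medians.

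**Algebra.** Substituting M_t = M_0 + dM and E_t = E_0 + dE gives

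dQ = (dE - Q_0 × dM) / M_t.

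So dQ depends on the baseline quotient and the follow-up morning level as well as on dM and dE. If one level rises and the other falls, the direction of dQ follows from their signs. If both move the same way, the direction depends on Q_0.

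**Check 1: levels move, quotient does not.**

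- Morning/evening 10/2 to 5/1: dM = -5, dE = -1; Q goes from 2/10 = 0.200 to 1/5 = 0.200, so dQ = 0.
- 10/2 to 15/3: dM = +5, dE = +1; Q goes from 0.200 to 3/15 = 0.200, so dQ = 0.

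**Check 2: the same level changes, different quotient changes.** Take dM = -2 and dE = -1 throughout.

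| Baseline M/E | Follow-up M/E | Q_0 | Q_t | dQ |
|---|---|---|---|---|
| 10/2 | 8/1 | 0.200 | 0.125 | -0.075 |
| 10/5 | 8/4 | 0.500 | 0.500 | 0 |
| 10/8 | 8/7 | 0.800 | 0.875 | +0.075 |

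The formula agrees: the numerator is -1 + 2 × Q_0, which changes sign at Q_0 = 0.5.

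**Check 3: group medians.** Three girls all start at 10/2. Their morning changes are -4, 0 and +4. Their evening changes are -0.8, 0 and +0.8 in some order, so the median dM and the median dE are both 0 in every row.

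| Evening changes, in the order of morning changes -4, 0, +4 | dQ for the three girls | Median dQ |
|---|---|---|
| -0.8, 0, +0.8 | 0, 0, 0 | 0 |
| 0, +0.8, -0.8 | +0.133, +0.080, -0.114 | +0.080 |
| +0.8, -0.8, 0 | +0.267, -0.080, -0.057 | -0.057 |

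The result depends on how morning and evening changes pair within girls, and separate medians discard that pairing.

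**The case against.** The best defence is that the sentence merges two intended analyses: change in the quotient, and change in each component. The stated purpose of sampling ("To measure the morning and evening components of the cortisol circadian rhythm") gives the separate level changes a legitimate role. The article also commits to calculating each girl's quotient, so the right change score is one subtraction away. And it is a condensed account; the full protocol or an analysis plan may set the matter out properly.

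Much of this stands. The level changes are relevant in their own right, and the authors may well have meant both. But the sentence gives the level changes as the means of studying the quotient, and the article nowhere states the quotient difference. An unseen document might repair this; it would not make the printed sentence correct.

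Three stronger readings are tempting and are not supported.

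- *A reader might infer that the level changes will point the opposite way from the quotient.* With two level changes and one ratio, opposite has no clear meaning. If morning goes from 10 to 12 and evening from 2 to 1, both changes push the quotient down, and it does fall, from 0.200 to 1/12 = 0.083. What is shown is narrower: when both levels move the same way, they do not settle the direction of the quotient.
- *A reader might infer that equal median level changes in the two arms are compatible with any difference in quotient.* The group example spans -0.057 to +0.080 on assumed values. Nothing beyond that has been shown, and the article gives no values from which to show it.
- *A reader might infer that the trial's main conclusion is at risk.* The primary outcome is reduced maximal pain on the diary at 8 months, and the Sample Size section rests on that alone. Cortisol enters neither.

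**Conclusion.** The point holds as an internal contradiction in one secondary analysis: the stated rule does not produce the stated quantity. That conclusion needs only the article's own definition of the quotient and elementary algebra.

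The size cannot be estimated. The illustrations prove that the two quantities can differ, including in direction, but they rest on invented levels. Whether the girls' baseline quotients and changes fall where the difference matters cannot be judged from the document.

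The consequence is limited. Cortisol is one of several secondary outcomes and sits beside questionnaire items on stress. Both samples are collected, so the correct score can be derived from the same data. The text should be corrected before the cortisol data are analysed, but the defect does not threaten the trial's primary result.

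**What to change.** Replace the change-score sentence with two statements.

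1. For each girl, the change score is the quotient at 4 months minus the quotient at baseline, and the quotient at 8 months minus the quotient at baseline. It is summarised by the median in each arm and compared between arms.
2. Changes in morning level and in evening level from baseline to 4 and 8 months are reported as separate analyses, labelled as changes in level.

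This keeps the plan's own quotient and its median. The difference in log quotients (log evening minus log morning, follow-up minus baseline) is an optional alternative. It changes the effect measure from a difference to a ratio of quotients, so it is a matter of choice and is not needed to remove the contradiction.

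The cost is two sentences. No new samples, assays or visits are required, and the article still describes the assay in the future tense, so on its own account the correction can precede the results.

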#### Feces Analyses

Participants received a kit containing everything needed to perform the fecal test at home. The test was stored in the freezer at home for approximately 1 week and was subsequently delivered to the research team in a small freezer bag. The samples are stored at –80 ⁰C at the university hospital in Örebro, and analyses of the intestinal microbiota and short-chain fatty acids will be performed.

#### Analyses of Physical Activity

The frequency of the accelerometer collecting data will be set to 30 Hz. Data will be processed in ActiLife (version 6.13.4; ActiGraph). Raw data from the accelerometers will be converted to 10-second epochs. Valid wear time will be considered to be at least 480 minutes per day, and minimum valid days will be set to 4 days, including 2 weekdays and 1 weekend day. Total counts per day, sedentary time, and activity of moderate or higher intensity will be measured.

#### Qualitative Analyses

The interviews will be transcribed verbatim and analyzed with inductive content analysis, as described by Elo and Kyngäs [109]. The analysis process will initially include getting to know the material, generating codes, and identifying categories. Data will be analyzed using the NVivo software program (QSR International) for qualitative data analysis [110]. All of the authors will discuss the coding process until it is agreed upon and the codes will be grouped into subcategories that reflect the core message of the interviews. Thereafter, the subcategories will be abstracted into generic and main categories [109].

#### Health Economic Analysis

The health economic evaluation will be performed as a cost-utility analysis using individual data [111]. Societal costs (including health care, informal care, and school health care) will be considered. Gained quality-adjusted life-years (QALYs) will be used to measure the effects. QOL will be measured with Kidscreen-10 [104], and an algorithm for mapping the Kidscreen-10 index onto the CHU9D utility scores will be used [105]. Questions about resource use and QOL are asked to both girls and their legal guardians at all follow-ups. Cost-effectiveness ratios will be based on the changes in QALY and net costs for the intervention group compared with the control group. The results will be presented as an incremental cost-effectiveness ratio (ICER), which is expressed as ICER = (Ca – Cb)/(Ea – Eb), where “Ca” is the cost of the intervention, Cb is the cost of the comparator, Ea is the effectiveness of the intervention, and Eb is the effectiveness of the comparator.

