### Study Design

This study, called Just in TIME (Try, Identify, Move, and Enjoy), started in 2016 when the first intake was performed and will end in 2023. The study is a prospective randomized controlled trial with 2 parallel groups—an intervention group and a control group—of girls aged 9 to 13 years with functional abdominal pain, IBS, or both. The intervention consists of dance and yoga sessions 2 times a week for 8 months. The control group receives standard care as school health care or primary care. The outcomes are measured at baseline and after 4, 8, 12, and 24 months. A long-term follow-up will be performed 5 years from baseline (Figure 1). At all follow-ups, data are collected for both the intervention and control groups. The trial is being conducted in 2 cities in Sweden.

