#### Randomization

When the baseline measurement was completed and the eligibility check was accomplished, the sample was randomized into an intervention group and a control group. Randomization was performed by an external statistician using minimization based on pain intensity and age at baseline [78].

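### The ICER rests on changes in QALY between arms with no stated conditioning on baseline utility; a baseline-adjusted QALY difference would cost almost nothing and be more precise

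*Protocol article*

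**What the plan says.** Under Health Economic Analysis: "The health economic evaluation will be performed as a cost-utility analysis using individual data". On the effect measure: "Gained quality-adjusted life-years (QALYs) will be used to measure the effects". On utility: "an algorithm for mapping the Kidscreen-10 index onto the CHU9D utility scores will be used". On the comparison: "Cost-effectiveness ratios will be based on the changes in QALY and net costs for the intervention group compared with the control group". The ICER is then defined in the usual way, with Ea − Eb as its denominator. The section names no covariate, regression or baseline term. It also does not say how the QALYs are accumulated, over what horizon, or whether the word changes means change from baseline or the increment between arms.

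Three other places bear on this:

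- **Study Design:** "The outcomes are measured at baseline and after 4, 8, 12, and 24 months". A baseline Kidscreen-10 is therefore implied. The economic section itself says only: "Questions about resource use and QOL are asked to both girls and their legal guardians at all follow-ups". The schedule by instrument is in Figure 2, which could not be read here.
- **Randomization:** "Randomization was performed by an external statistician using minimization based on pain intensity and age at baseline". Utility is not among the factors.
- **Statistical Analysis:** the only baseline-adjustment rule belongs to the mixed model for change scores. It covers only differences found significant at baseline, and it is not linked to QALYs.

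**The concern.** Baseline utility is the first point of each girl's utility curve and is correlated with the later points. An arm that starts higher by chance will tend to accumulate more QALYs whatever the treatment does. Subtracting the baseline in full does not cure this: when the correlation between visits is below 1, subtraction over-corrects and the error changes sign. Only conditioning on the baseline value removes the dependence in expectation under a linear model.

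The error lands in the denominator of a ratio, where a modest shift can move the ICER considerably if the true QALY difference is small. The same omission gives up precision that the data already collected could provide, in a trial that allocated 121 girls against a target of 150.

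**Working it through.** The article gives no utility SD, QALY difference or ICER, so there is no stated figure to reproduce. The check asks how much of a baseline gap reaches Ea − Eb, and what adjustment saves.

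**Inputs from the article.** Allocation 64 and 57 (Results); visits at 0, 4, 8, 12 and 24 months (Study Design).

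**Assumptions.** Equal SD at every visit; the same correlation ρ between any two visits, from 0.3 to 0.7; trapezoidal area under the curve; 12-month horizon; all allocated girls followed; utility SD 0.05 to 0.15 (absolute shifts only).

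**1. Size of a chance baseline gap.** SE = SD × √(1/64 + 1/57) = SD × √0.03317 = 0.182 SD. The 95% range is ±1.96 × 0.182 = ±0.357 SD.

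**2. How much of the gap reaches the QALY difference.** The 12-month trapezoidal weights at 0, 4, 8 and 12 months are 1/6, 1/3, 1/3 and 1/6, summing to 1.

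- Raw area: c = 1/6 + ρ × 5/6 QALY per unit of gap.
- Change from baseline: c − 1.
- Regression on baseline utility: 0 in expectation.

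**3. Variance of one girl's QALYs, in units of SD².** The sum of squared weights is 10/36 = 0.278.

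- Raw: V = 0.278 + ρ × 0.722.
- Change from baseline: V − 2c + 1.
- Adjusted: V − c² (ignoring the small cost of estimating the slope).

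| ρ | Gap passed on, raw | Gap passed on, change | Var raw | Var change | Var adjusted | Removed vs raw | Removed vs change |
|---|---|---|---|---|---|---|---|
| 0.3 | +0.417 | −0.583 | 0.494 | 0.661 | 0.321 | 35% | 51% |
| 0.5 | +0.583 | −0.417 | 0.639 | 0.472 | 0.299 | 53% | 37% |
| 0.7 | +0.750 | −0.250 | 0.783 | 0.283 | 0.221 | 72% | 22% |

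The percentages do not depend on the utility SD.

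**4. Other horizons, ρ 0.3 to 0.7.** Over 8 months the gap passed on is +0.32 to +0.52 (raw) or −0.35 to −0.15 (change). Over 24 months it is +0.72 to +1.45 or −1.28 to −0.55.

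**5. Absolute shifts, 12 months.** For SD 0.05 to 0.15, a gap of one SE is 0.009 to 0.027 in utility. Across ρ 0.3 to 0.7 it moves the raw QALY difference by 0.004 to 0.021, and the change version by 0.002 to 0.016 in the opposite direction. At SD 0.15 and ρ 0.5, the standard error of the QALY difference is 0.182 × 0.15 × √0.639 = 0.0218 raw, 0.0188 as change and 0.0149 adjusted. At SD 0.05 each is one third of that.

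**6. The significance-triggered rule.** If the mixed model's rule were borrowed for QALYs, gaps up to about 0.357 SD would normally go unadjusted. At ρ 0.5 and SD 0.15 such a gap shifts the raw difference by 0.357 × 0.15 × 0.583 = 0.031 QALY.

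**The case against.** The strongest reply is that this is a journal article which condenses the whole cost-utility analysis into one paragraph, and that covariates for incremental QALYs are commonly left to a full health economic plan. A reader might infer that the investigators have chosen an unadjusted comparison. The text does not support that: it never says unadjusted, and the ICER formula accepts an adjusted increment just as well. A reader might also infer that a baseline gap enters the denominator undiluted and in one known direction. That fails too, because the wording about changes in QALY can be read as change from baseline, and the remaining error then has the opposite sign.

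Other parts of the reply also stand. Randomisation makes the unadjusted difference unbiased on average. Minimising on pain may balance utility in part, as far as the two are correlated, so 0.182 SD may be somewhat high. Against that, the 20% dropout expected under Sample Size would raise it to 0.182/√0.8 = 0.204 SD. The SD, ρ and horizon are assumptions, and the section plans no significance test on QALYs, so power is not a suitable measure of the loss.

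What the reply does not remove is that the section does name an effect measure and a between-arm comparison. On either way of computing them a chance gap carries through, and the only baseline rule elsewhere in the article is of the wrong kind for this purpose.

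**Conclusion.** The point holds as a recommendation to improve a secondary economic analysis. It does not show an error in a stated figure, a biased estimator or a decision against adjustment. As the effect term is described, a chance baseline utility gap (SE 0.182 SD with 64 and 57 girls) would carry into Ea − Eb, in a direction that depends on how changes in QALY is read. For ρ 0.3 to 0.7 over 12 months, conditioning on baseline utility removes 35% to 72% of the variance of the raw version, or 51% to 22% of that of the change version. These percentages rest on the assumed correlation pattern and horizon. The absolute QALY shifts also rest on an assumed SD. Whether the ICER would cross any cost-effectiveness threshold cannot be judged from the article, which gives neither a threshold nor an expected QALY difference.

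**What to change.** In Health Economic Analysis, state that each girl's QALYs are the area under her mapped utility curve. Estimate Ea − Eb as the arm coefficient from a regression of QALYs on arm, baseline mapped utility, baseline pain intensity and age. The last two are the minimisation factors. Keep these terms whether or not the arms differ significantly at baseline. Use this estimate as the ICER denominator and report the unadjusted difference as a sensitivity analysis.

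This also settles the ambiguity over changes in QALY. With complete data, the arm coefficient is the same whether the outcome is the raw area or the area minus baseline, once baseline utility is in the model.

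The cost is a sentence or two in the plan and one regression on data that the schedule implies are already held. Confirm first that Kidscreen-10 was taken at baseline. The report needs a short note that the ICER uses an adjusted difference.
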